## Abstract

**Trial registration:**

ClinicalTrials.gov, identifier: NCT05605951.

## Introduction

Optic neuritis (ON) is the most common optic neuropathy in young adults with an annual incidence rate of three to five per 100,000 person-years (1–4). ON involves primary inflammation, demyelination, and axonal injury in the optic nerves and the chiasm (1, 5). This can lead to retinal ganglion cell destruction and significant visual loss (4, 6). ON can be the initial event in multiple sclerosis (MS), including clinically isolated syndrome (CIS) (3), in aquaporin-4-IgG positive (AQP4-IgG+) and seronegative neuromyelitis optica spectrum disorders (NMOSD) (7), and in myelin oligodendrocyte glycoprotein-IgG (MOG-IgG+)-associated disease (MOGAD) (8). The incidence of ON is stable and similar around the world (4, 9), but the proportion of ON patients with AQP4-IgG+ON and MOG-IgG+ON vs. MS-ON differs greatly in different races (4). Visual outcomes vary between the three diseases (10): in MS-ON and MOG-IgG+ON, visual prognosis is good (10–13), but AQP4-IgG+ON is associated with significant visual loss (11, 14–16). As the three disease entities require different acute and long-term treatment strategies, earlier diagnostic stratification has the potential to assist tailored treatment decisions and thereby improve visual outcomes (17).

The Acute Optic Neuritis Network (ACON) is a global cooperation of 28 academic centers longitudinally investigating subjects with inaugural acute ON (Figure 1). Here, we present the protocol for the ACON study, which primarily aims to evaluate the effect of time to corticosteroid treatment (measured as the number of days from onset of visual loss to treatment with high-dose corticosteroids; *days-to-Rx*) on visual and structural outcomes in MS-ON, AQP4-IgG+ON, and MOG-IgG+ON respecting the novel diagnostic criteria for ON (18).

**Figure 1 F1:**
[figure not shown]
Participating ACON centers. Twenty-eight ACON centers (status 10/2022) Africa (Botswana, Zambia), Asia (India, Korea, Thailand, Vietnam), the Middle East (Israel), North America (USA), South America (Argentina, Brazil, Colombia), Australia, and Europe (Denmark, France, Germany, Italy, Spain, United Kingdom).

### The effect of hyperacute high-dose corticosteroid treatment on functional outcome in inaugural MS-ON, AQP4-IgG+ON, and MOG-IgG+ON

Current treatment protocols for ON are based on the landmark 1992 Optic Neuritis Treatment Trial (ONTT), which involved 457 patients with new onset ON. The trial included three arms: placebo, 250 mg of IVMP every 6 hours for three days followed by oral prednisone at 1 mg/kg for 11 days, and oral prednisone at 1 mg/kg for 14 days (19). As treatment with IVMP was associated with a more rapid recovery of visual function and showed the most benefit within the first 15 days of follow-up, many centers used this protocol to treat people who present with ON. Importantly, the inclusion criteria stipulated that people with visual loss in the preceding 8 days could be enrolled in the ONTT (19), and the subsequent results of the ONTT showed that there was a delay in initiation of the treatment (mean 5 days ± 1.6 days) (19, 20). The ONTT was not designed to investigate the impact of time from visual loss or indeed the preceding pain to high-dose corticosteroid therapy. The ONTT was conducted prior to the advent of the serological tests for AQP4-IgG and MOG-IgG. On subsequent testing of all the ONTT participants, it did not contain any patients with AQP4-IgG+ON and only a few patients with MOG-IgG+ON (21). The recommendations formed by this landmark article are limited by the inclusion criteria and are likely of limited applicability in countries and across races where the proportion of AQP4-IgG+ON and MOG-IgG+ON is higher, as compared with North America. Preliminary evidence from several retrospective studies suggests a benefit to visual outcomes of initiating early high-dose corticosteroids to treat AQP4-IgG+ON and MOG-IgG+ON (20, 22–25). We propose verifying the functional benefit of early high-dose corticosteroids in a global, multi-racial prospective study including patients with inaugural MS-ON, AQP4-IgG+ON, and MOG-IgG+ON.

### Developing data for ON escalation treatment protocols

There is currently no consensus on escalation treatment protocols for protocols for plasma exchange (PLEX) or intravenous immunoglobulines (IVIG) in the treatment of antibody-mediated ON and a lack of specific recommendations with respect to treatment duration. With no prior studies analyzing the varying patterns of ON severity, the speed of disease progression, the degree of response to high-dose corticosteroids, and the difficulty in comparing patients presenting late vs. early after the onset of visual loss, all of which make treatment escalation guidelines difficult to develop. The development of this study and the detailed database, which accurately captures ON severity and course, builds the basis for the development of treatment escalation guidelines.

### Structural biomarkers as an aid to tailor ON treatment

To explore possible means to aid hyperacute treatment decisions, the ACON study will collect data on and evaluate the potential of structural biomarkers as methods to enhance timely diagnoses. These structural biomarkers will be explored using magnetic resonance imaging (MRI) and optical coherence tomography (OCT).

MRI of the brain and the orbits is one of the most established clinical tools for investigating acute ON. The radiological features of ON differ between the three disease etiologies: optic nerve lesions in AQP4-IgG+ON and MOG-IgG+ON are more frequently bilateral and more extensive than in MS-ON (26–28). AQP4-IgG+ON typically affects posterior parts of the optic nerve and the chiasm, while MOG-IgG+ON typically affects long segments of the anterior optic nerve (10, 28). During the acute phase of ON, optic nerve lesion length has been shown to be a useful imaging biomarker, predictive of retinal neuro-axonal loss and chronic visual impairment (29). We will explore the diagnostic and clinical relevance of visual pathway lesions and their persistence following the inaugural ON.

OCT with the peripapillary retinal nerve fiber thickness (pRNFL), the macular ganglion cell layer (GCL), or the ganglion cell complex (GCC) measurements aid differentiation between acute MS-ON and MOG-IgG+ON (30). However, age and race have been reported to impact pRNFL (31). We will re-explore whether pRNFL robustly differentiates MS-ON from MOG-IgG+ON in a multi-racial population of subjects with inaugural ON. Assessment of OCT imaging parameters such as the ganglion cell analysis may allow disease stratification and detection of subclinical activity prior to the initial ON and may provide insightful longitudinal data such as rate of progression, which has the potential to correlate with disease severity (32, 33).

### Biological biomarkers

Neurofilament light chain (NfL) is a major structural component of neurons and can be detected in the serum and cerebrospinal fluid (CSF). Elevated NfL levels are an indicator of neuronal damage (34) in acute ON (35), coinciding with visual dysfunction (36) and structural retinal damage (37). However, the role of serum NfL levels and dynamics in the acute stage of ON as potential indicators for subsequent conversion to MS, NMOSD, or MOGAD remains unexplored.

Glial fibrillary acidic protein (GFAP) is the predominant intermediate filament in mature astrocytes (38, 39) and was identified in astrogliosis MS lesions (40). It is differentially elevated in the CSF and the blood in the three inflammatory diseases of interest in this study (41–43). ACON aims to collect data on NfL and GFAP in the serum and CSF of patients following acute ON and to investigate their patterns in MS-ON, AQP4-IgG+ON, MOG-IgG+ON and also in double-seronegative non-MS-ON.

The detection of serum MOG-IgG is a crucial step for correctly diagnosing MOGAD (44). Live cell-based assays (CBA) using full-length human MOG are optimal and have consistently shown a 99% specificity for typical MOGAD phenotypes (44, 45). Many centers worldwide use a commercially available cell-based assay using fixed transfected cells (Euroimmun AG, Lübeck Germany), which has excellent (98%) specificity (46). Titers of MOG-IgG can decrease to undetectable levels following an acute attack, after treatment or disease remission. Thus, potential factors affecting the duration of seropositivity will be explored using longitudinal serum samples from patients exhibiting MOG-IgG seropositivity following acute ON. The diagnostic value of CSF antibody testing remains unclear. Since AQP4-IgG and MOG-IgG are both produced extrathecally, testing CSF is currently not routinely recommended (47). However, a few cases of seronegative NMOSD have been described, where MOG-IgG was present in CSF only (48). ACON aims to clarify the role of MOG-IgG in CSF in double-seronegative non-MS-ON.

### Clinical phenotypes

Pain patterns differ between MS-ON, AQP4-IgG+ON, and MOG-IgG+ON. Typically, both MS-ON and AQP4-IgG+ON are preceded by relatively mild retrobulbar pain, which worsens with eye movement (1, 49–51). By contrast, pain in MOG-IgG+ON is typically intense (52, 53). No comparative studies to date have investigated pain scoring to distinguish MS-ON and AQP4-IgG+ON from MOG-IgG+ON.

Measurements of visual function in daily routine and quality of life (QoL) are understudied in neuroscience, though of great value to patients. Issues impacting QoL after an ON event include perceived visual dysfunction, the degree of anxiety regarding future loss of vision and further relapses, pain patterns, depression, and adjustment difficulties. Visual function in daily routine correlates with functional (e.g., visual acuity) and structural measurements (e.g., pRNFL) of visual outcome in NMOSD (16). The long-term visual function in daily routine and Qol following ON is an understudied aspect, which may be explored through a high-quality detailed database of questionnaires filled in by patients in a prospective fashion.

In summary, ACON will build a broad dataset to serve as a platform to revise and tailor acute ON treatment recommendations, improve the differential diagnoses between neuroimmunological disease entities, and identify determinants of disease progression and QoL in subjects after inaugural MS-ON, AQP4-IgG+ON, and MOG-IgG+ON.

## Methods and analysis

### Study objectives

The primary objective of ACON is to investigate whether MS-ON, AQP4-IgG+ON, and MOG-IgG+ON patients treated with early high-dose corticosteroids for visual loss have better visual outcomes than those with late treatment. Treatment with both IVMP and oral high-dose corticosteroids is currently used as the standard of care in ON and will be included. According to previous data (24), subjects will be stratified into three groups: those presenting within 3 days of the onset of visual loss, those presenting between 4 and 7 days from the onset of visual loss, and those presenting between 8 and 30 days from onset of visual loss (days-to-Rx). The stratification will be performed within each respective disease group (MS, AQP4-IgG+NMOSD, and MOGAD).

Secondary objectives will consist of the interaction between clinical and para-clinical parameters, as well as their association with patient-reported QoL aspects (see Table 1; Figure 2).

**Table 1 T1:** Secondary objectives.

• Visual and structural outcomes of acute ON in patients treated with high-dose corticosteroid-therapy vs. plasmapheresis as first-line treatment.
• Visual and structural outcomes of MS-ON in patients treated with high-dose corticosteroid-therapy with oral prednisone taper vs. without taper as standard of care.
• Diagnostic and prognostic value of biomarker levels (NfL, GFAP) and associations with visual pathway damage (MRI- and OCT-based) in the acute stage and during follow-up.
• Characterization of MOG-IgG and AQP4-IgG levels and compartmentalisation (serum vs. CSF, using simultaneous paired samples) and associated risks for subsequent relapses in subjects with AQP4-IgG+ON and MOG-IgG+ON.
• Diagnostic value of OCT markers (e.g., increased pRNFL) for diagnosis of MS, NMOSD, and MOGAD.
• Prognostic value of OCT markers (e.g., increased pRNFL) for the visual outcome at 12-months follow-up.
• Diagnostic value of OCT markers for a conversion from acute ON to clinically definite MS.
• Diagnostic value of early clinical variables (i.e., visual loss and pain patterns).
• Investigation of the link between clinical symptoms (i.e., degree of visual loss and pain patterns) and lesion extension (detected using MRI and OCT).
• Characterization of visual function in daily routine, visual QoL scores and incidence of depression at 12-months follow-up.
• Interrelation of HC-BCVA and LC-BCVA and patient reported outcome measures at 6- and 12-months follow-up.

AQP4, aquaporin-4; CSF, cerebrospinal fluid; GFAP, glial fibrillary acidic protein; HC-BCVA, high-contrast best-corrected visual acuity; LC-BCVA, low-contrast best-corrected visual acuity; MOG, myelin-oligodendrocyte glycoprotein; MRI, magnet resonance imaging; MS, multiple sclerosis; NfL, neurofilament light chain; NMOSD, neuromyelitis optica spectrum disorders; OCT, optical coherence tomography; ON, optic neuritis; pRNFL, peripapillary retinal nerve fiber layer; QoL, quality of life.

**Figure 2 F2:**
[figure not shown]
Flowchart of ACON study design. ACON, Acute Optic Neuritis Network; AQP4, aquaporin-4; CSF, cerebrospinal fluid; days; f/u, follow-up; GFAP, glial fibrillary acidic protein; MRI, magnet resonance imaging; MOG, myelin-oligodendrocyte glycoprotein; NEI-VFQ-25, National Eye Institute Visual Function Questionnaire; NfL, neurofilament light chain; OCT, optical coherence tomography; ON, optic neuritis; QoL, quality of life; y, years.

### Study design

ACON is an international, multicenter non-interventional study network aiming to optimize treatment decisions in subjects with acute ON and to improve understanding of the underlying pathologies. It currently includes 28 teaching hospitals from Africa (Botswana, Zambia), Asia (India, Korea, Thailand, and Vietnam), the Middle East (Israel), North America (USA), South America (Argentina, Brazil, and Colombia), Australia, and Europe (Denmark, France, Germany, Italy, Spain, and United Kingdom) (for details see Supplementary material).

ACON centers will recruit and prospectively collect data from all subjects with inaugural acute ON (see study population).

Local staff will have confirmed up-to-date training in the conduct of studies according to the International Conference on Harmonization of Technical Requirements for Registration of Pharmaceuticals for Human Use (ICH) and good clinical practice (GCP) standards.

All study participants will be evaluated during hospitalization or through outpatient clinics at the time of presenting with inaugural acute ON as well as during follow-ups (at 6- and 12-month after onset). Visits at additional time points are optional, based on patient-tailored needs and the recruiting centers' standard of care. The recruitment period is planned for 36 months. Acute ON treatment is provided as part of routine care according to the clinical best practice at the respective study center. This study will not include the randomization of patients to receive early or late high-dose corticosteroids. Disease diagnosis will be assessed at 6- and 12-month follow-up visits, respecting the diagnostic criteria for MS according to the 2017 revised McDonald criteria (54), diagnosis of AQP4-IgG-positive or seronegative NMOSD according to the 2015 international consensus diagnostic criteria (55), and diagnosis of MOGAD in subjects with clinical characteristics consistent with MOGAD and positive testing of MOG-IgG with respect to the new MOGAD diagnostic criteria (44, 56, 57).

### Study population

A total of 300 patients with acute ON will be screened for study eligibility. We will include only patients with inaugural ON. Subjects presenting for the first time with isolated ON or ON with additional demyelinating syndromes, e.g., myelitis or acute disseminated encephalomyelitis (ADEM) occurring within 30 days of the acute ON, will be included. Furthermore, patients with dissemination in time and space on MRI will be included. Patients with prior soft symptoms, which can retrospectively be considered to be a demyelinating manifestation will be included, excluding patients with a prior demyelinating diagnosis or prior symptoms of optic neuritis (see exclusion criteria). The prevalence of MS-ON, AQP4-IgG+ON, and MOG-IgG+ON differs in each of the participating centers. For the primary analysis, we collect data from subjects with MS-ON, AQP4-IgG+ON, and MOG-IgG+ON. For the secondary analysis, multimodal data will be collected in subjects with any demyelinating ON (CIS-ON, MS-ON, AQP4-IgG+ON, or MOG-IgG+ON and seronegative non-MS-ON) with the aim of exploring clinical, structural, and laboratory biomarkers to expedite the diagnosis and tailoring of treatment. This data will include OCT measurements, an MRI of the visual pathway including orbital cuts, questionnaires (headache, visual function in daily routine, depression, and QoL), basal metabolic index (BMI), IVMP, and oral corticosteroid treatment duration, utility of escalation therapy with PLEX or IVIG, and serum and CSF biomarkers (AQP4- and MOG-IgG levels, NFL, and GFAP).

We expect between 30 and 50% of subjects will be ineligible due to the rigorous exclusion criteria.

The inclusion criteria include written informed consent, age ≥18 years, and diagnosis of an inaugural ON with respect to the novel diagnostic criteria for ON (18) within 30 days from the onset of visual loss and in the absence of previously diagnosed demyelinating events.

The exclusion criteria comprise other forms of optic neuropathy (e.g., glaucoma, Leber's hereditary optic neuropathy, other inherited optic neuropathies such as OPA1/OPA3-mutations, granulomatous, infectious, infiltrative, or toxic neuropathies, as well as incidental signs of prior optic neuropathy, prior events of visual loss, and clinical evidence of optic nerve thinning at presentation), other significant comorbidities (i.e., medically uncontrolled severe arterial hypertension, severe diabetes mellitus, chronic infectious diseases, drug abuse, and severe psychiatric or psychological disorders), prior demyelinating diagnosis, pregnancy at inclusion, MRI contraindications, and medical or psychological constraints impacting the ability to give informed consent to study participation and fulfill the study protocol.

The inclusion and exclusion criteria are summarized in Table 2. They are applied at the time of screening by the study physician. Throughout the study duration, we will apply drop-out criteria (see Table 2) as a guideline to evaluate the case for a premature end-of-study.

**Table 2 T2:** Inclusion and exclusion criteria.

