### Sample size considerations

The study is exploratory, and therefore, a formal sample-size computation is not possible. Hence, we justify the sample size by feasibility, which is *n* = 100 for MS-ON and *n* = 50 for AQP4-IgG+ON and MOG-IgG+ON. For each disease (MS-ON, AQP4-IgG+ON, and MOG-IgG+ON), patients will be stratified into subgroups according to the number of days since the onset of visual loss: 0–3 days, 4–7 days, and 8–30 days until high-dose corticosteroid treatment. With *n* = 50, the width of the 95% confidence interval for the treatment effects (=difference between visual acuities between these strata) is ~0.55 standard deviations of the mean difference depending on the actual number of patients within each subgroup.

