### Statistical analysis

For data analysis, subjects will be assigned into groups according to their diagnosis at the 6-month follow-up. For the primary objective, data from subjects with a diagnosis of MS, AQP4-IgG+ NMOSD, and MOGAD will be analyzed. Data from subjects with other diagnoses (other autoimmune, e.g., CIS-ON, seronegative non-MS-ON) will be described and characterized separately but not included in the primary analysis.

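### Screening 300 with 30–50% ineligible leaves 150–210 patients, so the stated 200 is reached only near the favourable end and with almost no further removal

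*Protocol article*

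**What the plan says.** All references are to the protocol article.

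- **Study population**, on recruitment: "A total of 300 patients with acute ON will be screened for study eligibility". It adds: "We expect between 30 and 50% of subjects will be ineligible due to the rigorous exclusion criteria".
- **Sample size considerations**, on size: "Hence, we justify the sample size by feasibility", "which is *n* = 100 for MS-ON and *n* = 50 for AQP4-IgG+ON and MOG-IgG+ON". Patients are then split by days to treatment within each disease, and precision is quoted at n = 50: "the width of the 95% confidence interval for the treatment effects (=difference between visual acuities between these strata) is ~0.55 standard deviations".
- **Study population**, on who is enrolled: "multimodal data will be collected in subjects with any demyelinating ON (CIS-ON, MS-ON, AQP4-IgG+ON, or MOG-IgG+ON and seronegative non-MS-ON"). CIS-ON and seronegative patients are therefore in the study and are not among the ineligible.
- **Statistical analysis**, on who counts: "subjects will be assigned into groups according to their diagnosis at the 6-month follow-up". Patients with other diagnoses, such as CIS-ON and seronegative non-MS-ON, "will be described and characterized separately but not included in the primary analysis".

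The article gives no expected share of other diagnoses. Table 2 lists drop-out criteria, but no drop-out rate is given. Nothing links the 300 screened to the 200.

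**The concern.** The plan offers feasibility as the only support for its group sizes, so the recruitment figures have to be able to produce them. Over most of the plan's own range of ineligibility they cannot. Part of the enrolled cohort is then set aside by design before the primary analysis.

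What is at stake is precision. The width of the confidence interval is quoted for n = 50 in a disease group. If the groups are smaller, the diagnosis-specific contrasts between timing strata are less precise than a reader of the plan would expect. No stated power is lost, because none is claimed.

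**Working it through.** **Inputs from the article.** Screened: 300. Ineligible: 30–50%. Stated sizes: 100, 50 and 50.

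**Step 1: is it 50 for each antibody group?** The full width of a 95% interval for one mean from 50 patients is 2 × 1.96 / √50 = 0.554 SD, which matches the quoted ~0.55. The strata are also formed within each disease. Both support 50 per antibody group, so the stated total is 100 + 50 + 50 = 200.

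**Step 2: eligible patients.** Eligible = 300 × (1 − ineligible share), assuming that every eligible patient is enrolled.

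| Ineligible | Eligible | Against 200 |
|---|---|---|
| 30% | 300 × 0.70 = 210 | +10 |
| 33.3% | 300 × 0.667 = 200 | 0 |
| 40% | 300 × 0.60 = 180 | −20 |
| 50% | 300 × 0.50 = 150 | −50 |

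The break-even point is 1 − 200/300 = 33.3%. The part of the range above it is (50 − 33.3)/(50 − 30) = 0.83, about five-sixths.

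**Step 3: room for further removal.** At 30% ineligible the surplus is 10 of 210, so CIS-ON, seronegative and unclassified or lost patients together may be at most 1 − 200/210 = 4.8% of those enrolled. At 33.3% there is no room.

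**Step 4: yield and screening number for an assumed removal share.** Yield = 300 × (1 − ineligible) × (1 − removed). Screening number = 200 / [(1 − ineligible)(1 − removed)], rounded up. The removal shares are assumptions, because the article gives none.

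| Removed (assumed) | Yield at 30 / 40 / 50% ineligible | Screened to reach 200 |
|---|---|---|
| 0% | 210 / 180 / 150 | 286 / 334 / 400 |
| 10% | 189 / 162 / 135 | 318 / 371 / 445 |
| 20% | 168 / 144 / 120 | 358 / 417 / 500 |
| 30% | 147 / 126 / 105 | 409 / 477 / 572 |

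**Step 5: effect on precision, for illustration.** Assume that the 2:1:1 mix holds and that the three timing strata are equal. A total of 150 gives 150/4 = 37.5 per antibody group, or 12.5 per stratum, against 50/3 = 16.7 per stratum at n = 50. The full 95% width for a difference between two strata, in SDs of visual acuity, is 2 × 1.96 × √(2/m), with m patients per stratum:

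- n = 50: 2 × 1.96 × √(2/16.7) = 1.36
- n = 37.5: 2 × 1.96 × √(2/12.5) = 1.57

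The ratio is √(50/37.5) = 1.15, so the interval is about 15% wider. Both widths are calculated here and are not the plan's. They should not be set against its ~0.55, which step 1 reproduces as the width for a single mean. Whether ~0.55 is the right width for a contrast is a separate question.

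**The case against.** Several counter-arguments carry some weight.

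- **The range includes 200.** At 30–33.3% ineligible the eligible count alone is 200–210. A reader might infer that the plan cannot deliver 200 at all. The article does not support that: in this part of the range a shortfall needs removals above 0–4.8%, and no removal rate is stated. This stands and limits the claim.
- **Who bears the shortfall.** A reader might also infer that it falls on the antibody-positive groups because they are smallest. Nothing in the article shows this. It says only that prevalence differs between centers. Under a constant 2:1:1 mix every group shrinks by 25% at a total of 150, and MS-ON loses as many patients (25) as the two antibody groups together.
- **Loss before 6 months.** The article assigns groups by the 6-month diagnosis but has no rule for a patient without that visit. Antibody samples are taken early, and diagnosis is also assessed at 12 months. Removal of such patients is a reasonable reading but not a stated rule.
- **300 may not be a cap.** Study design has centers recruiting all patients with inaugural acute ON over 36 months, and the section on potential bias cites a poll of centers as evidence of feasibility. The flowchart (Figure 2) cannot be seen. None of the visible text reconciles 300 with 200, but it leaves room for 300 to be an expectation.
- **50 might cover both antibody groups together.** The target would then be 150, just met at 50% ineligible with no removal. The stratification within each disease and the precision quoted at n = 50 speak against this reading.
- **The study is exploratory.** No test or success criterion depends on reaching 200. This lowers the severity. It does not remove the conflict, because feasibility is the only justification given for the sizes.

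**Conclusion.** The inconsistency holds in limited form. From the article's own figures alone, the total is short of 200 whenever more than 33.3% are ineligible, by 20 at 40% and by 50 at 50%. Below that point, 200 is attainable only if other diagnoses and loss stay within 4.8% of those enrolled at best. That is little room in a design that deliberately enrols patients it will not use in the primary analysis.

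The total of about 105–189 rests on an assumed removal of 10–30%. The 15% widening rests on a total of 150, a 2:1:1 mix and equal strata. The estimand, the model and the validity of the primary estimate are unaffected. This is a planning inconsistency that should be fixed, below the level of a mandatory correction.

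**What to change.** Reconcile Study population with Sample size considerations in one of two ways.

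1. **Keep 300 screened.** Restate the primary-analysis sizes that it can give (at most 150–210 in total, before other diagnoses and loss), with expected shares for both and the precision that follows.
2. **Keep 100 + 50 + 50.** Say that 300 is not a cap and state the screening number as 200 / [(1 − ineligible)(1 − removed)]. This is 286–400 with no other removal, and about 318–572 if 10–30% are removed (assumed).

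The first costs only wording, and the stated sizes and precision become less favourable. The second also commits centers to more screening if the plan's ineligibility range is right. Neither changes the analysis model or patient care.
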